### Recruitment, randomization, and data collection (visit 0)

During the selection visit (visit 0), all eligible patients will be advised that smokers are susceptible to various diseases related to tobacco use and smoking cessation will be recommended. They will then be told about the study and offered the possibility of participating. Those who agree will be asked to provide signed informed consent and all the necessary data will be collected using an ad hoc questionnaire that includes:Personal and sociodemographic data (age, sex, marital status, and education level and occupation as markers of social class)History of diseases, comorbidities, and drug treatmentsHistory of respiratory symptomsLifestyle (alcohol use and physical activity)Smoking habit, current and cumulative (packs/year); nicotine dependence (Fagerström test [29]), motivation to quit smoking (Richmond test [30]), and stage of change (precontemplation, contemplation, preparation, action, maintenance and relapse, according to Prochaska and DiClemente [31])Previous quit attempts (number and therapeutic resources used)Basic physical examination (weight, height, body mass index, blood pressure)eCO levels, measured by MicroCO™ (Micro Medical Ltd, Rochester, UK); this model detects an eCO concentration range of 0-100 parts per million (ppm) with a sensitivity of 1 ppm.

All health professionals working in the 20 primary care centers included in this study will be eligible to participate in the selection process.

#### Randomization

After the selection visit, included participants will be randomized 1:1 to the intervention or control group. The group assignment will be blinded, consecutive, and centralized at the Tarragona Research Support Unit of the IDIAP Jordi Gol, and will follow a simple randomization numeric sequence compiled for this purpose. Of course, due to the nature of the intervention, researchers and participants cannot be blinded to this assignment.

#### Data collection

Individuals assigned to the intervention group will be contacted to return to their primary care center for an evaluation of their pulmonary function using forced spirometry. The test will be carried out by selected nursing personnel with the appropriate technical skills accredited by the Health Studies Institute of the Catalan government, all using the same standard model of spirometer (DATOSPIR-600, SIBEL SA, Barcelona, Spain) with a disposable LILLY-type transducer and following a standard procedure according to ATS/ERS (American Thoracic Society/European Respiratory Society) recommendations [32].

At least three tests will be carried out, from which the best values will be selected for forced vital capacity (FVC), expiratory flow in the first second (FEV1), and ratio of the two measures (FEV1/FVC). Variability between these two tests should be <5 %, expiration time >6 seconds, and the start of the test should show an appropriate and rapid increase. Finally, the reversibility of a possible airway obstruction will be evaluated by a repeat spirometry test 20-30 minutes after the administration of 400 micrograms of salbutamol using a space chamber. All of the tests will be submitted to a single observer, who will centralize quality control and interpret the results using computer software.

### Description of the intervention (visit 1)

All participants will be contacted for an intervention (visit 1) that will include a 5-minute session with their doctor, who will provide health education and advice about quitting smoking, following the usual recommendations for primary care professionals provided by the Tobacco Study Group of the Catalan Society of Family Medicine and the special program, “Atenció Primària Sense Fum” (in Catalan; “Smoke-Free Primary Care”), as shown in Table 2. In addition, they will receive information about the ill effects of tobacco on pulmonary function, illustrated by the Fletcher diagram showing how age-related loss of lung capacity can be accelerated in smokers and how this deterioration slows when one quits smoking, although lost capacity is not recovered [33].

**Table 2 Tab2:** Summary of the RESET study control and intervention protocols

Control group: brief anti-smoking intervention	Intervention group: spirometry report
In a 5-minute intervention, the health professional will make a clear, firm, personalized proposal recommending smoking cessation, in an empathic and respectful manner. He or she will clearly explain to the smoker that the most important decision the individual can make to achieve better health is to quit smoking, and will provide written informational materials that describe the benefits of giving up smoking.	In a 15-minute intervention, the health professional will carry out an intervention with the same content as the brief anti-smoking intervention and will provide personalized information about the spirometry results, clearing up any patient doubts about spirometry or any other questions that come up during the visit.
The materials are provided by the “Smoke-Free Primary Care” program of the Catalan Society of Family Medicine and the Public Health Agency of Catalonia and are regularly used in primary care offices for brief anti-smoking interventions.	If spirometry values are within normal range, the patient will be informed that his or her pulmonary function has not yet deteriorated and that this would be a good time to quit smoking.
	If spirometry values indicate airway obstruction (FEV1/FVC <70 %), the patient will be informed that he or she could have chronic obstructive pulmonary disease due to smoking, and that the most important treatment measure is to quit smoking.
	If spirometry values show airway restriction, the patient will be informed that his or her pulmonary function could be affected and will be advised to continue with the pulmonary tests normally administered in that primary care center.
	In addition, the patient will be informed of his or her lung age (i.e., the mean age of a nonsmoker with the same FEV1) compared to his or her chronological age, in order to illustrate the possible deterioration of the lungs as a result of smoking.

In addition, participants assigned to the intervention group will receive standardized information about their spirometry results in a personalized visit lasting about 15 minutes, explaining the content of the report in detail. The commentary on each spirometry test will be prepared from a consensus interpretation by the research team, and will focus on a structured description of the results obtained and their interpretation with reference to a theoretical normal value. In addition, the participant will be informed about the “lung age index”, defined as the mean age of a nonsmoker with the same FEV1 value), compared to the chronological age of the participating smoker. This will illustrate the pulmonary deterioration that occurs as a consequence of smoking tobacco [34]. Patients with FEV1 and/or FVC values <80 % of the theoretical reference value and/or FEV1/FVC <0.7 will be informed and advised to undergo the medical testing required to confirm a possible problem with pulmonary function.

Independently of study group assignment, all participants who indicate a desire to quit smoking will be offered the possibility of attending the quit-smoking consultations that are integrated into the everyday activities at each center.

### Follow-up period (visits 2-3)

All participants will be periodically evaluated by their regular primary care team. This will include two follow-up telephone calls, at 3 months (visit 2) and 6 months (visit 3) postintervention, to determine whether they have quit smoking or have made changes in their smoking habits. New data will be collected on current consumption or quit date, if that is the case.

Finally, an in-person visit will be scheduled with each participant (visit 4) after 12 months have passed since study inclusion. At this last study visit, data will again be collected about smoking habits (current consumption, nicotine dependence, motivation and stage of change), attempts to quit, and resources and drug therapy used during the 12-month follow-up. Participants who report that they have quit smoking will be asked to provide their quit date, and their non-smoking status will be confirmed by measuring eCO levels and urine cotinine.

### Definition of variables

#### Outcome measures

The primary outcome variable will be prolonged abstinence at 12 months postintervention. The secondary variable will be point-prevalence abstinence at the end of follow-up. The criterion used to establish the type of abstinence will follow the recommendations of the Society for Research on Nicotine and Tobacco [35]:Prolonged abstinence, defined as sustained abstinence from an initial period in which smoking is not counted as a failure (the recommendation is that this period not exceed 2 to 4 weeks) until a follow-up point.Point-prevalence abstinence refers to abstinence during a time window immediately before the follow-up point (usually 7 days).

Self-reported smoking abstinence will be validated by biochemical testing at the end of follow-up. Only those participants who report that they quit smoking and have eCO levels less than 10 ppm and urine cotinine values less than 100 ng/mL will be considered nonsmokers [36].

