#### Independent measures

The predictive variables to be analyzed include the following:Demographic: age, sex, and social class (education level and occupation)Anthropometric (weight and height) and main spirometry parameters (FVC, FEV1, and FEV1/FVC%)History of comorbidities and risk factors associated with tobacco use (hypertension, diabetes mellitus, ischemic heart disease, cerebrovascular accident, peripheral arterial disease, etc.)Lifestyles and habits (physical activity, use of alcohol or other drugs)Characteristics of the smoking habit (accumulated and current consumption, stage of change [Prochaska], score on dependency test [Fagerström], and motivation [Richmond]), previous quit attempts and reasons for relapse, and use of drug therapy or other methods to quit smoking during the year of follow-up.

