### Limitations of the study

The study has several potential limitations that must be taken into consideration. The first cluster is related to the population. Participants were volunteers recruited when they visited their primary care team for any reason; therefore, they might not be representative of the population of smokers in the primary care system. In addition, those who agreed to participate could be more motivated to quit smoking than the rest of the population of smokers. In any case, the proposed randomization should ensure comparability between study groups. As patients will be recruited by a health care professional with whom they have an existing relationship, participation is expected to be high, especially considering that no drug therapies or invasive or unpleasant tests are involved. Nonetheless, a certain percentage of losses to follow-up is to be expected because this is a long-term (12-month) project. To minimize this contingency, sustained effort by all participating researchers will be essential to motivating and encouraging patients.

With respect to limitations of the study design, the most obvious is that a double-blind study is impossible; both participants and investigators will necessarily be aware of the study group assignments. The proposed intervention may be less intensive than has been described in other studies, but reflects the usual attention received by smokers and therefore can be readily incorporated into the daily clinical practice of the investigators. The content and duration of the intervention have been standardized and participating doctors and nurses will receive specific training to ensure that similar messages, attitudes, and behaviors will be applied in interactions with both groups. In the spirometry intervention group, patient collaboration and technical considerations will be key to achieving quality results. To maximize quality, the testing will be standardized by the use of high-quality pneumotachography and by training of study personnel that results in official accreditation. In addition, to reduce variability in the interpretation of results, data analysis will be centralized.

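### The abstinence rule makes no exception for self-reported quitters using a nicotine-containing cessation product at visit 4, so some smoke-free participants may be scored as smokers

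*Protocol article*

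**What the plan says.** Under Outcome measures, "The primary outcome variable will be prolonged abstinence at 12 months postintervention"; the secondary variable is point-prevalence abstinence at the end of follow-up. Both concern smoking, not nicotine intake. A participant counts as abstinent only on reporting having quit and meeting both biochemical limits: those who "have eCO levels less than 10 ppm and urine cotinine values less than 100 ng/mL will be considered nonsmokers". No alternative is given for anyone.

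The section Follow-up period (visits 2-3) says who is tested. For participants who report at visit 4 that they have quit, "their non-smoking status will be confirmed by measuring eCO levels and urine cotinine". Table 1 places both tests at 12 months.

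Three places bear on cessation aids:
- Description of the intervention (visit 1): in either arm, participants who want to quit "will be offered the possibility of attending the quit-smoking consultations that are integrated into the everyday activities at each center".
- Follow-up period (visits 2-3): visit 4 collects "attempts to quit, and resources and drug therapy used during the 12-month follow-up".
- Independent measures: the predictors include "use of drug therapy or other methods to quit smoking during the year of follow-up".

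Limitations of the study remarks that "no drug therapies or invasive or unpleasant tests are involved". In context this describes what taking part involves. It does not bar participants from using cessation drugs, and the two places that record such use confirm that reading.

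**The concern.** Cotinine is a metabolite of nicotine, whatever the source of the nicotine. Someone who has stopped smoking but is using a nicotine product when the urine sample is taken can therefore reach 100 ng/mL without having smoked. Under the rule as written, that person is a treatment failure on both abstinence outcomes. The article collects information on drug therapy, but the outcome definition makes no use of it.

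Within each arm the error runs one way: it removes true abstainers and adds none. At stake are the absolute difference and the number needed to treat (NNT), both planned results under Statistical analysis, and the hypothesis itself, which is framed as an absolute gain of 5% or more. If spirometry feedback led more people in one arm to nicotine products, the RR would be distorted as well.

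**Working it through.** **Inputs from the article (Sample calculation).** 500 per arm; control abstinence 5% to 6%; difference 5 percentage points; two-sided 5% level; 80% power; about 10% loss. Evaluable per arm: 500 × 0.90 = 450.

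**Input not in the article.** f is the share of true abstainers who use a nicotine product at visit 4 and have urine cotinine of 100 ng/mL or more. No figure is given. I assume 2% to 10%, and show 20% as an outer case.

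**The plan's own figure.** With a pooled-variance comparison of two proportions,

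n = [1.96·√(2·p̄·(1−p̄)) + 0.8416·√(p1(1−p1) + p2(1−p2))]² / (p2−p1)², then n / 0.90:

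| Control vs intervention | n per arm | After 10% loss | Total |
|---|---|---|---|
| 5% vs 10% | 435 | 484 | 968 |
| 5.5% vs 10.5% | 461 | 513 | 1026 |
| 6% vs 11% | 488 | 543 | 1086 |

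The stated 1000 is reproduced to within 3% at the midpoint of the control range. The sample size is not in dispute.

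**Effect of the rule.** Observed rate = p × (1 − f). Power = Φ{[|p2−p1|·√450 − 1.96·√(2·p̄·(1−p̄))] / √(p1(1−p1) + p2(1−p2))}, using the observed rates. Here 5% and 10% are taken as true rates before verification.

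For f = 10% in both arms: 0.05 × 0.90 = 4.5% and 0.10 × 0.90 = 9.0%, a difference of 4.5 points. With p̄ = 0.0675 the argument of Φ is (0.9546 − 0.6954) / 0.3534 = 0.733, so power is 76.8%.

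| f, both arms | Observed rates | Difference (points) | RR | NNT | Power, 450 per arm |
|---|---|---|---|---|---|
| 0% | 5.0% vs 10.0% | 5.0 | 2.00 | 20.0 | 81.4% |
| 2% | 4.9% vs 9.8% | 4.9 | 2.00 | 20.4 | 80.5% |
| 5% | 4.75% vs 9.5% | 4.75 | 2.00 | 21.1 | 79.2% |
| 10% | 4.5% vs 9.0% | 4.5 | 2.00 | 22.2 | 76.8% |
| 20% (outer case) | 4.0% vs 8.0% | 4.0 | 2.00 | 25.0 | 71.5% |

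NNT = 1 / difference. At 6% versus 11%, power is 76.8% with no misclassification, 75.9% at f = 2% and 72.0% at f = 10%.

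**In people.** At 5% versus 10% the expected abstainers are 450 × 0.05 = 22.5 and 450 × 0.10 = 45. With f = 10%, about 2 control and 4 to 5 intervention abstainers would be reclassified; with f = 2%, about 0.5 and 0.9.

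**Unequal f (illustration only).** With 5% in control and 10% in intervention, the observed rates are 4.75% and 9.0%: difference 4.25 points, RR 1.89, power 71.3%. Reversed, they are 4.5% and 9.5%: difference 5.0 points, RR 2.11, power 83.8%. The direction of any bias in the RR depends on which arm uses more, which the article does not say.

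**The case against.** **Nicotine replacement is not named.** The article speaks of consultations and drug therapy in general. The nicotine products in its Background belong to earlier Italian and Belgian trials, and the same text mentions bupropion, which contains no nicotine. This stands: that such use is allowed is an inference from the absence of a ban and from the recording of drug therapy.

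**Timing.** Drug use at any time in 12 months is not use at visit 4. Prolonged abstinence allows an initial grace period that should not exceed 2 to 4 weeks. If that period runs from visit 1, a primary-outcome success has been smoke-free for about 11 months and may well have stopped nicotine products. This stands too, and makes the concern weaker for the primary outcome than for point-prevalence abstinence, where a quit can be recent.

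**The planning rates may already be verified rates.** The sample calculation does not say. If they are, the power loss computed above does not arise in that form, although individuals can still be misclassified.

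**Strictness is defensible in an open trial.** Requiring both tests guards against false claims of quitting, and an eCO-only route could be opened by a false claim of nicotine-product use. This is a real cost, but keeping the strict rule as a sensitivity analysis exposes it.

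**The article is condensed.** Details may sit in a fuller document. That does not answer the point, because the article states a complete rule that excludes everyone who does not meet both limits.

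A reader might infer that all participants face the cotinine test, that continuing nicotine users are to be expected in number, or that power falls to about 62%. The documents support none of these. Only self-reported quitters are tested, and no rate of use is given. The 62% figure needs 5% of control and 15% of intervention abstainers to be affected (4.75% versus 8.5%, power 61.9%), a threefold imbalance with no basis in the text.

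**Conclusion.** The point holds in a limited form. The rule as written would score a smoke-free user of a nicotine product as a smoker if cotinine reaches 100 ng/mL, and the design leaves room for such users in both arms. The error lowers observed abstinence. Equal misclassification shrinks the absolute difference and raises the NNT without moving the RR; only unequal misclassification biases the RR, in a direction the documents do not settle.

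The size is uncertain and may be small. The range of 4.9 to 4.5 points, with power of 80.5% to 76.8% instead of 81.4%, rests on three assumptions: that 2% to 10% of abstainers are affected in both arms, that the planning rates precede verification, and that 450 per arm are evaluable. This is a worthwhile improvement to the endpoint definition, not a flaw that undermines the trial.

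**What to change.** At visit 4, ask self-reported quitters whether they used any nicotine-containing product in the past 7 days. The existing item on drug therapy over the whole year does not establish use at the time of the sample. In the endpoint definition, classify self-reported abstainers who answer yes by eCO below 10 ppm alone, and keep both criteria for all other quitters. Prespecify the both-tests rule for all quitters as a sensitivity analysis, and report by arm how many participants change category.

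The cost is one question and one sentence, with no change to treatment, visits or sample size. There are two downsides. eCO alone is less sensitive to light or non-recent smoking. In an open-label trial, nicotine-product use could also be misreported differently by arm; the sensitivity analysis and the counts by arm would show how far the result depends on this.

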#### Independent measures

The predictive variables to be analyzed include the following:Demographic: age, sex, and social class (education level and occupation)Anthropometric (weight and height) and main spirometry parameters (FVC, FEV1, and FEV1/FVC%)History of comorbidities and risk factors associated with tobacco use (hypertension, diabetes mellitus, ischemic heart disease, cerebrovascular accident, peripheral arterial disease, etc.)Lifestyles and habits (physical activity, use of alcohol or other drugs)Characteristics of the smoking habit (accumulated and current consumption, stage of change [Prochaska], score on dependency test [Fagerström], and motivation [Richmond]), previous quit attempts and reasons for relapse, and use of drug therapy or other methods to quit smoking during the year of follow-up.

### Data recording and storage

All of the information from the study will be recorded consistently on an ad hoc questionnaire designed for this purpose. Each participant will be assigned a personal identification code upon inclusion, consisting of the initials of their surnames, sex, and birthdate. All information obtained will be stored using an online application accessible only from the Intranet of the Catalan Health Institute in Tarragona. Access to this site is restricted and will be controlled by a personal password for each investigator, who will be responsible for data entry for all of the participants he or she recruits. Weekly back-ups will provide two secure copies of all stored data.

### Statistical analysis

Data for the present study were extracted from a centralized database and grouped so that the person responsible for their analysis was blinded to study group assignments. First, the database was cleansed by detecting and labeling outlier, missing, and inappropriate values. Next we tested the effectiveness of the randomization by evaluating the comparability and homogeneity of the study groups to ensure similar distribution of the variables of interest at baseline. Finally, the proportion of participants lost to follow-up in each group was determined and tested for any association with the study intervention. All analysis was based on intention to treat, understood as having recorded relevant data on the primary variable at the participant’s first visit. Worst-case analysis was applied to assess potential bias due to losses to follow-up [37], which considers that the desired outcome was obtained by all participants lost to follow-up who were in the control group and by none of those lost from the intervention group. Having made this assumption, we repeated the analysis and, to determine the variability associated with the losses to follow-up, compared the “worst-case” results and the results obtained when those lost to follow-up were not taken into account.

Descriptive analysis of quantitative and qualitative variables included frequencies, central tendencies (mean or, in the case of non-normal distribution, median) with standard deviation, and minimum and maximum values. Frequencies were compared using chi-square test or Fisher exact test, as appropriate, and means using Student t test for independent samples.

To evaluate the effectiveness of the smoking cessation intervention, rates of punctual and prolonged abstinence were assessed at 12 months post-intervention in both groups using the chi-square test. The results were presented as relative risk (RR), relative risk reduction (RRR) and absolute risk reduction (RAR) and number needed to treat (NNT) to achieve prolonged smoking abstinence in one smoker, expressed with their 95 % confidence interval (CI). To study the behavior of both groups over time, log-rank tests were used to compare the cumulated abstinence curves over the 12-month follow-up. Finally, multivariate analysis using Cox regression was applied to study the factors associated with smoking cessation success at 12 months. Various models were formulated that included the variable of interest (the described interventions) and as control variables the factors shown to be most significant in the literature [38]: age, sex, social class, employment status, educational level, daily and cumulated tobacco use, degree of nicotine dependence, degree of motivation to quit smoking, and stage of change.

All analysis was done using SPSS version 19.0. Significance was set at *p* < 0.05.

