**Methods/Design:**

We propose a multicenter randomized clinical trial in the primary care setting. **Study subjects**: We will recruit active smokers of both sexes, aged 35-70 years, with a cumulated smoking habit exceeding 10 packs/year and who consult for any reason with their primary care physician in the 20 health centers in the province of Tarragona (Spain). Patients with a history of lung disease or who have undergone exploratory measures of pulmonary function in the preceding 12 months will be excluded. All patients who agree to participate will provide signed informed consent prior to their inclusion. A total of 1000 smokers will be consecutively randomized to a control or intervention group (1:1). **Intervention:** Participants in both groups will receive brief (5-minute) health counseling, in accordance with usual clinical practice. In a consultation lasting about 15 minutes, participants in the intervention group will also receive detailed, personalized information about the results of a spirometry test and about their lung age compared with their chronological age. Both groups will be followed up for 12 months. **Main variables and analysis:** The main variable will be sustained smoking abstinence at 12 months after the intervention, as confirmed by CO breath testing and urine cotinine test. Results will be analyzed based on intention to treat, using the chi-square test and logistical regression if necessary to adjust for confounding variables.

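### The primary comparison is an unadjusted chi-square, valid but slightly inefficient, and no single adjusted effect estimate on the visit-0 predictors of quitting is fixed in advance

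*Protocol article*

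**What the plan says.** **Primary test.** The Statistical analysis section states that "rates of punctual and prolonged abstinence were assessed at 12 months post-intervention in both groups using the chi-square test". Relative risk, absolute risk reduction and number needed to treat are reported alongside.

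**Adjusted analyses.** Two are mentioned:
- The Abstract plans the analysis "using the chi-square test and logistical regression if necessary to adjust for confounding variables".
- The Statistical analysis section says that "multivariate analysis using Cox regression was applied to study the factors associated with smoking cessation success at 12 months". It adds: "Various models were formulated that included the variable of interest". Ten control variables follow, described as "the factors shown to be most significant in the literature". They include daily and cumulated tobacco use, dependence, motivation and stage of change.

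**Baseline data.** At visit 0 every participant gives current and cumulative consumption, a Fagerström score, a Richmond score and a stage of change (Recruitment, randomization, and data collection). Allocation comes after that visit and "will follow a simple randomization numeric sequence compiled for this purpose". No stratification is stated.

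**Sample size.** The plan is 500 per group, for a difference of 5% or more with 80% power in two-tailed tests. It assumes control abstinence of 5% to 6% and about 10% loss (Sample calculation).

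**The concern.** With a binary outcome expected in roughly one participant in twelve, the information lies in a small number of quitters. The plan collects the variables that it regards as the main predictors of quitting, on everyone and before allocation, and then leaves them out of the primary estimate. Simple randomisation does nothing to balance them either. An adjusted estimate on the same risk-difference scale would answer the same question with somewhat less variance.

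The adjusted analyses that are planned do not fill this place. One depends on an unstated judgement of necessity, made in a plan that first tests the groups for baseline comparability. The other is a family of models aimed at identifying factors associated with success. The two also name different regressions. If the chi-square result is borderline, nothing fixed in advance says which adjusted estimate of the intervention effect should be read.

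**Working it through.** **1. Reproduce the plan's sample size.** Inputs from Sample calculation and Statistical analysis: two-sided alpha 0.05, power 80%, difference 5 percentage points, control rate 5-6%, loss 10%.

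n per arm = [1.96·√(2p̄(1−p̄)) + 0.8416·√(p1(1−p1)+p2(1−p2))]² / (p2−p1)², then divided by 0.90.

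At 5% vs 10%: [1.96·√0.13875 + 0.8416·√0.1375]² / 0.0025 = 435 when rounded up. Then 435/0.90 = 484 per arm, or 968 in total.

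Power with 450 per arm (500 × 0.90) = Φ{[0.05·√450 − 1.96·√(2p̄(1−p̄))] / √(p1(1−p1)+p2(1−p2))}. Expected quitters = 450·(p1+p2).

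| Control vs intervention | n per arm | Total after loss | Power, 450 per arm | Expected quitters |
|---|---|---|---|---|
| 5% vs 10% | 435 | 968 | 81.4% | 67.5 |
| 5.5% vs 10.5% | 461 | 1026 | 79.0% | 72.0 |
| 6% vs 11% | 488 | 1086 | 76.8% | 76.5 |

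The stated 1000 is reproduced at the midpoint of the control range. Counting losses as smokers (500 per arm, both rates multiplied by 0.9) changes little: 81.0%, 78.7% and 76.4%.

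**2. Effect of adjustment.** The article gives no prognostic strength, so the AUC is an assumption and is varied. Trials of 450 per arm were simulated. The variance ratio is the variance of the risk difference standardised from the adjusted logistic model, divided by that of the crude difference. Power compares the chi-square with the Wald test for arm in the adjusted model.

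| Model | Assumed AUC | Variance ratio, 5% vs 10% | Variance ratio, 6% vs 11% | Power at 6% vs 11%, chi-square → adjusted |
|---|---|---|---|---|
| 4 covariates, 6,000 trials | 0.65 | 0.987 | 0.980 | 0.775 → 0.781 |
| | 0.70 | 0.968 | 0.953 | 0.762 → 0.779 |
| | 0.75 | 0.945 | 0.934 | 0.767 → 0.793 |
| 10 covariates, 3,000 trials | 0.61 | 1.001 | 1.006 | 0.769 → 0.775 |
| | 0.68 | 0.976 | 0.972 | 0.780 → 0.784 |
| | 0.75 | 0.939 | 0.932 | 0.783 → 0.818 |
| | 0.82 | 0.874 | 0.894 | 0.772 → 0.825 |

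A further simulation of the estimator proposed below (standardised risk difference, five covariates) gave variance ratios of about 0.99, 0.96 and 0.91-0.94 for weak, moderate and fairly strong predictors. Power gains were about 0-4 points and type I error was 4.6-5.5%.

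**3. Analytic cross-check at 6% vs 11%.** If the covariates explain a share R² of the outcome variance, the effective size is 450/(1−R²) per arm. R² = 0.02 gives 77.6%, 0.05 gives 78.9% and 0.08 gives 80.2%, against 76.8% unadjusted. With an outcome this rare, an AUC of 0.75 corresponds to an R² of only about 0.08, which is why the gain is small.

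**4. Type I error.** In the null simulations rejection was 4.3-5.6% across methods. In the four-covariate run it was 5.3% unadjusted and 4.9% adjusted. With 3,000 trials the Monte Carlo standard error is √(0.05·0.95/3000) = 0.4 points, so the methods do not differ detectably.

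**5. How many covariates the data support.** Fagerström, Richmond, cigarettes per day and stage of change in three levels cost five parameters, six with arm: 67.5/6 to 76.5/6, about 11-13 quitters per parameter. All ten listed factors at one parameter each would leave 67.5/10 to 76.5/10, about 7-8, before counting arm.

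**The case against.** The strongest reply is that nothing here is an error. A chi-square with the absolute difference and relative risk is a valid primary analysis under simple 1:1 allocation, it matches the two-proportion sample size, and there are no stratification factors that the analysis must respect. That stands in full. A reader might infer that chance imbalance biases the primary result. It does not: with 500 per arm the standard deviation of a standardised baseline difference is about √(2/500) = 0.06, and the test's error rate already allows for it.

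Secondly, adjustment is planned. A reader might infer from the chi-square alone that the visit-0 predictors go unused. The documents do not support that, since the Cox models contain the intervention together with all four. What remains is narrower: those models are multiple, the logistic alternative is conditional, and neither is designated as the effect estimate.

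Thirdly, the predictors may be weak. The article cites their standing in the literature but gives no AUC, R² or odds ratio, so calling them strong would go beyond it. At an AUC of 0.61 the gain is nil.

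Finally, an analysis plan not shown may settle the details. That would answer a complaint about missing detail. It does not alter the choice of primary test, which the article itself states.

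**Conclusion.** The point holds as a modest loss of efficiency, together with the absence of one designated adjusted estimate. It is not an invalid analysis. Over an assumed AUC of about 0.65 to 0.75, with 450 evaluable per arm and a 5-point effect, the variance of the risk difference falls by about 1-9% and power rises by about 0-4 points. A gain of 5-6 points would need an AUC near 0.82, for which the article offers no support.

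A reader might also infer that adjustment would make good the power shortfall at a 6% control rate. It does so only at the favourable end: adjusted power there ran from 0.779 to 0.793 with four covariates, and reached 0.818 with ten only at an AUC of 0.75. The change is worth making because it costs almost nothing and settles in advance which adjusted estimate counts. The trial does not depend on it.

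**What to change.** Prespecify as the primary estimate the risk difference, with the relative risk, in 12-month prolonged abstinence, standardised from one logistic model. Include arm, Fagerström score, Richmond score and cigarettes per day (linear), and stage of change in three levels. Visit 0 lists six stages, so state the collapsing rule. Use visit-0 values only, and keep the set whatever the baseline comparison shows.

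Leave out spirometry values, which the Data collection section places after allocation and in the intervention group only. Also leave out drug therapy during follow-up, which is a post-randomisation variable. Both appear under Independent measures.

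Retain the chi-square as a supportive analysis, label the Cox models as exploratory, and bring the Abstract's wording into line.

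The cost is one paragraph of analysis text and minor programming, with no new data or participants. The downsides are small: a model replaces a two-by-two table, and a simple rule is needed for missing baseline values.
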